**Methods:**

This study will use a quasi-experimental design (target *N* = 412) to examine potential gains in CSA-related awareness and intentions to use protective behaviors among parents who participate in a universal parent-focused CSA prevention workshop, *Smarter Parents*. *Safer Kids*., compared to those who do not. Participants in both the control (*n* = 206) and experimental group (*n* = 206) will complete 3 survey assessments: Survey 0 (baseline), Survey 1 (1-month), and Survey 2 (3-month follow-up). The experimental group will participate in a *Smarter Parents*. *Safer Kids*. workshop between the Surveys 0 and 1. We will use data collected from the baseline to measure potential mediators of CSA-related awareness and intention to use protective and preventive behaviors. In adjacent efforts to enhance the curriculum’s reach with future dissemination and implementation, we will also explore the impact of recruitment materials and strategies on parental engagement.

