### 1.3. Current study

Next in the line of research to establish an evidence base for *Smarter Parents*, the current study will capitalize on the active implementation of *Smarter Parents* by nine community-based partners across the Commonwealth of Pennsylvania–referred to as Project Safe and Smart. This study will therefore use a quasi-experimental design (target *N* = 412) to examine potential gains in CSA-related awareness (i.e., knowledge of and attitudes toward appropriate CSA prevention strategies) and intentions to use protective behaviors among parents who participate in *Smarter Parents* compared to those who do not (Aim 1). Then, we will consider potential mediators of CSA-related awareness and protective behaviors (e.g., demographic characteristics, initial parenting strategies, use of protective and preventive behaviors; Aim 2). Lastly, we will also explore the impact of recruitment materials and strategies on parental engagement (i.e., workshop registration and attendance; Aim 3). Results of this study will contribute to the growing evidence base of *Smarter Parents* and will advance efforts to implement universal CSA prevention with parents and primary caregivers.

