### 2.4. Measures

At Survey 0, participants will be asked to provide basic demographic characteristics (i.e., age, number of children, level of educational attainment). The primary outcome of interest, parents’ CSA-related awareness and parent behaviors will be assessed using the Assessment of SmartParents’ Knowledge (ASK) [18]. The 15-item ASK, rated on a 5-point Likert scale (i.e., Strongly Disagree to Strongly Agree), provides an indicator of parents’ CSA-related awareness (e.g., “Most sexual abuse victims are abused by someone they know”) and intention to use protective behaviors (e.g., “I have talked to my child about how to protect themselves from being sexually abused”).

To explore CSA-related preventive behaviors used by the parent, at Survey 0 all parents will be asked to complete the 10-item preventive behaviors questionnaire (PBQ) [30]. On the PBQ, parents to report how frequently in the past month (i.e., never [0], sometimes [1–5 times a month], or a lot [6–10 times a month]) they performed a named preventive behavior (e.g., “Educated [their] child about the difference between safe and unsafe touches” or “Modeled or talked about privacy in the home.”). The PBQ, thus, measures actual use of protective behaviors.

To examine general parenting modalities, all parents will be asked to complete the 16-item Knowledge of Parenting Strategies Scale (KOPSS) [31] at Surveys 0 and 1. The KOPSS asks parents a set of multiple-choice questions about parenting practices (e.g., “It is 5 minutes before dinner time and a child is throwing a tantrum for a cookie. What should mum do?”) and awards a parent one point per correct answer. Higher scores indicate a greater degree of use of desired parenting qualities.

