#### 2.6.2. Analytic plan

Quantitative analyses of the resulting pre- and post-workshop data will examine whether levels of CSA-related awareness and intention to use protective behaviors are greater for parents who participated in a Smarter Parents workshop in comparison to those who did not. As we will have longitudinal quasi-experimental data, we will use a difference-in-difference (DID) approach to analysis [38]. DID is appropriate when (a) randomization at the individual level is not possible and (b) the goal is to examine the effect of a specific intervention by comparing changes overtime among those who received the intervention (experimental) and those who did not (control). Using the DID regression framework, meditation analyses will examine potential differential effects by parent characteristics (e.g., demographics, initial parenting strategies [KOPSS] and actual use of protective and preventive behaviors [PBQ]).

To understand the impact of recruitment materials on parental engagement, we will first qualitatively code the strategies used on recruitment materials provided by the sites (e.g., theoretical framing, image, testimonial, incentive, etc.). We will quantify which strategies were used most consistently across the experimental site. We will also map types of ads used by the sites to registration/attendance numbers reported on the implementation forms. Participant responses on the satisfaction form (e.g., “Do you have any suggestions on how to promote Smarter Parents in your community?”) will be coded thematically to inform sites recruitment efforts in the future. All data will be made available in the lead authors’ university data repository once the study is complete.

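### Aim 2 is labelled mediation, but every variable named for it is measured before the workshop and the question it states is moderation

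*Protocol article*

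**What the plan says.** Three places in the protocol article describe Aim 2.

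- Abstract, Methods: "We will use data collected from the baseline to measure potential mediators of CSA-related awareness" and of the intention to use protective behaviors.
- Section 1.3 sets out to study "potential mediators of CSA-related awareness and protective behaviors (e.g., demographic characteristics, initial parenting strategies, use of protective and preventive behaviors; Aim 2").
- Section 2.6.2, within the difference-in-difference (DID) regression framework: "meditation analyses will examine potential differential effects by parent characteristics". The examples given are "demographics, initial parenting strategies [KOPSS] and actual use of protective and preventive behaviors [PBQ"].

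The timing is fixed elsewhere. The abstract places the "workshop between the Surveys 0 and 1". Section 2.4 states: "At Survey 0, participants will be asked to provide basic demographic characteristics". It gives Survey 0 as the only time point for the preventive behaviors questionnaire (PBQ). It places the Knowledge of Parenting Strategies Scale (KOPSS) at Surveys 0 and 1, but Aim 2 and section 2.6.2 refer only to initial parenting strategies.

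**The concern.** A mediator is a variable that the intervention changes and that in turn changes the outcome. A value recorded before the workshop cannot have been changed by it. A baseline characteristic can predict the outcome, confound the group comparison or modify the effect, but it cannot mediate the effect.

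Mediation and moderation models estimate different quantities. A mediation model splits the effect into direct and indirect parts; a moderation model asks who benefits more. If the analyst follows the label, the second question goes unanswered.

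The design adds to the risk. Under section 2.3 the experimental group consists of workshop participants at nine partner sites, while controls answer general advertisements distributed by other agencies. Section 3 itself acknowledges possible selection bias. Baseline differences between the groups are therefore plausible, and a mediation model would report them as a pathway.

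**Working it through.** **Timing of each named variable**

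| Variable named for Aim 2 | When measured (section 2.4) | Relative to the workshop |
|---|---|---|
| Demographics | Survey 0 | before |
| Initial KOPSS | Survey 0 (the scale is repeated at Survey 1, but only the initial score is named) | before |
| PBQ | Survey 0 (no other time point in the text) | before |

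The schedule figure was not available for this check; the table rests on the text.

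**Label against question.** Section 2.6.2 names one class of analysis and, in the same sentence, asks whether effects differ by parent characteristics. That is effect modification. If moderation was the intended word there, the sentence is sound in itself but conflicts with the abstract and section 1.3, which both say mediators. Either way the three places need to be reconciled.

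**What a mediation model would return.** The indirect effect is a × b, where a is the group difference in the supposed mediator and b is that variable's association with the outcome given group. For a Survey 0 variable the workshop's contribution to a is zero, so the true indirect effect is zero. Whatever a is estimated to be, it is the baseline difference between the groups plus sampling error, and a × b carries that difference into the result.

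**The plan's own sample size, as a check on inputs.** Section 2.6.1 gives a pre-post correlation of .7, d = .2, alpha .10 and a need for 317 in total (158 per condition). It states neither power nor sidedness. With baseline-adjusted variance 1 − 0.7² = 0.51, two-sided alpha .10 (z = 1.645) and 80% power (z = 0.842):

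n per arm = 2 × 0.51 × (1.645 + 0.842)² / 0.2² ≈ 157.7, rounded up to 158, or 316 in total.

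This matches 158 per condition and is within one of 317, so 80% power and a two-sided test are used below as assumptions.

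**Illustration: size of interaction that could be detected.** Assume a binary moderator split 50/50. Each of the four cells holds n/2 parents, so the interaction has variance 4v/(n/2) = 8v/n and a standard error of √(8v/n). Here v is 0.51 (baseline-adjusted) or 2(1 − 0.7) = 0.60 (change score, as in a simple DID). The per-arm n is 158 (the plan's figure before attrition) or 144 (206 × 0.7 = 144.2, if the assumed 30% are lost). The detectable interaction is 2.487 × the standard error.

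| v | n per arm | Standard error | Detectable interaction (SD) | Power for 0.2 SD |
|---|---|---|---|---|
| 0.51 | 158 | 0.161 | 0.40 | 34% |
| 0.51 | 144 | 0.168 | 0.42 | 32% |
| 0.60 | 158 | 0.174 | 0.43 | 31% |
| 0.60 | 144 | 0.183 | 0.45 | 29% |

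The interaction's standard error is twice that of the main DID effect: at v = 0.60 and n = 144 the main effect has √(2 × 0.60/144) = 0.091.

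**The case against.** The best defence is that this is a wrong word on a correctly described analysis. The article never mentions indirect effects, paths or mechanisms. Its one operative sentence on Aim 2 asks for differential effects within a DID regression, and the natural way to estimate those is the interaction model recommended here. The abstract and section 1.3 speak of mediators of awareness and behaviors, not of the workshop effect, which fits loose use of the word for predictors or modifiers. Aim 2 is also worded tentatively and does not drive the sample size.

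Much of this stands. A reader might infer that Aim 2 is bound to give a wrong answer. The documents do not support that, because the operative wording already points to effect modification; the wrong model is a risk, not a certainty. A reader might also take the interaction figures as showing that the trial fails a promise. It makes no power claim for Aim 2, so they contradict no stated figure. They also rest on a binary moderator, whereas KOPSS and PBQ are multi-item scales and age and number of children are numeric.

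What does not stand is that the label is harmless or merely condensed. The article positively assigns a mediating role to variables that cannot have one, and nothing in its text corrects this.

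**Conclusion.** The concern holds as a contradiction between the analysis named for Aim 2 and both the variables and the question given for it. It rests only on the article's own timing and wording and needs no numerical assumption. It should be fixed before analysis, but it does not threaten the study's main result: the Aim 1 comparison and the sample size do not depend on it.

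The bias from fitting a mediation model cannot be sized from the article, because it depends on baseline differences not yet observed. The interaction range is illustrative. It indicates that, under the stated assumptions, only effect differences at least twice the d = .2 assumed for the main effect would be found reliably, which is reason to treat the moderation results as exploratory.

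**What to change.** 1. Replace mediator and mediation with moderator and moderation in the abstract, section 1.3 and section 2.6.2.
2. State in section 2.6.2 that Aim 2 will be tested with group × time × baseline-characteristic interactions in the DID regression, using Survey 0 demographics, KOPSS and PBQ, and that the results will be read as exploratory.
3. If mediation is also wanted, present it as a separate question with a variable measured after the workshop and before the outcome, such as Survey 1 KOPSS for a Survey 2 outcome. Acknowledge that this path too is open to confounding in non-randomised groups. The Assessment of SmartParents' Knowledge (ASK) at Survey 1 would be a poor mediator for the same instrument at Survey 2, since it is the outcome measured earlier.

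The cost is wording and model specification. No new data, visits or participants are needed.

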## 3. Conclusion

Though incidence rates of CSA in the U.S. have declined meaningfully since the 1990s [39], the most recent estimates suggest a prevalence rate of nearly 22% [40]. CSA remains a public health concern of considerable magnitude. Declining rates may be attributable to myriad CSA prevention efforts [41]; it is unlikely that a singular strategy focused on only one segment of the population will affect rates of CSA [42]. It is our belief that there is real potential to affect rates when parents and children alike have the tools to talk to each other. It is imperative that parents be included in primary prevention efforts [15]. The current study, while it does not use a randomized controlled trial design, advances the science of parent-focused CSA prevention by measuring actual use of protective behaviors and grows the evidence-base of universal CSA prevention efforts.

While this work was initially adapted from a selective prevention curriculum [19], universal prevention for parents regardless of risk is a crucial next step towards protecting all children from CSA. The perspective of the *Smarter Parents* curriculum, and this study, is that equipping all parents–regardless of risk level–with the knowledge and skills to protect their children from victimization is a crucial part of the prevention spectrum. It is understood that the nature of universal CSA prevention may introduce selection bias (i.e., wherein those at most risk may not opt to engage in such a program), however, this is inevitable with most any universal program and can be seen in selective prevention interventions as well [43, 44]. The benefits of universal prevention far outweigh its challenges [43]. Results of this quasi-experimental trial will contribute to the evidence base of *Smarter Parents*. *Safer Kids*. and take us one step closer to bringing parent-focused CSA prevention to a universal audience.
